## Assignment of interventions: blinding

### Who will be blinded {17a}

The participants assigned to the two tablet groups will be blinded to the intervention. The magnesium and placebo tablets that are used in the trial will be identical in terms of packaging and appearance. The compression stocking group cannot be blinded, but the participants will not know their allotted intervention until they have received it by mail delivery. The statisticians will be blinded to the group allocation by using codes to label the three groups and will randomly assign outcome assessors to the follow-up. The allocation sequence will be concealed until the end of the study. The allocation code will be stored in a separate file.

### Procedure for unblinding if needed {17b}

Each participant will have a personal identification code that is asked in every questionnaire of the study. The identification code acts as a link between the study material and the participants’ identifying information. The independent investigator who has done the randomisation will know the allocated intervention and can unblind it if needed in case of serious adverse effects.

## Data collection and management

### Plans for assessment and collection of outcomes {18a}

The study will last for 8 weeks (Figs. 1 and 2). During the first 4 weeks, the participants will observe the frequency of the manifestation of the cramps, the intensity of the cramps and the quantity of nocturnal awakening due to the cramps without any treatment. Information will be collected at the end of each week using an electronic questionnaire. A link to the questionnaire will be sent weekly by e-mail as a reminder. Participants will be requested to keep a tally of the leg cramps daily in order to improve the reliability of the results by minimising recall bias. The compression stockings, magnesium tablets and placebo tablets will be posted to the participants along with instructions for use. During the following 4 weeks, each of the participants will observe the incidence of the cramps, the intensity of the cramps and the quantity of nocturnal awakenings due to the cramps using the intervention that they have been sent in accordance with randomisation. The weekly reporting of the symptoms will continue using the same electronic questionnaire as previously. Any other symptoms, participant’s health or changes in the way of life will not be monitored during the follow-up.

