#### Exclusion criteria

Peripheral artery disease (confirmed or suspected).Peripheral artery bypass surgery.Grave peripheral neuropathy or any sensory disorder.Allergy to the material of the compression stockings.Grave renal failure (GFR under 30 ml/min).The use of a magnesium carbonate product (e.g. Rennie® or Berocca®).Cardiac failure with pulmonary oedema or massive lower limb swelling.Lower limb soft tissue problems, including skin transplant, thinned skin, varicose ulcer, necrosis and any infection.Lower limb deformity or atypical shape or size that could prevent the usage of compression stockings.Continuous usage of compression stockings for any other reason than leg cramps.

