### Criteria for discontinuing or modifying allocated interventions {11b}

The allocated intervention can be discontinued at any stage of the study in response to harm or the participant’s request. Possible harms are, for example, an allergy to the material of compression stockings, allergy to an ingredient of either magnesium or placebo tablets, magnesium-induced diarrhoea or inability to find suitable compression stockings. Participants can drop out of the study at any time for any reason without consequences. Any harms reported to the research assistant will be recorded. Allocated interventions cannot be modified.

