### Relevant concomitant care permitted or prohibited during the trial {11d}

The use of any magnesium products or compression stockings other than those used as the interventions of the study is prohibited during the trial. Any other medications and supplements in use will be recorded and should be continued regardless of the study.

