### Confidentiality {27}

Material for the study will be collected using electronic questionnaires. Participants will fill out the questionnaire themselves once every week for 8 weeks. The consent forms that contain the participants’ names, birth dates or social security numbers, addresses, phone numbers and e-mail addresses will be sent to the principal investigator and stored in a locked cabinet of a locked office at the Unit of General Practice at Tampere University. The study material will be stored separately on secured computers, and it will not contain any information that could reveal the identity of the participants. In addition, the contact information form will be stored separately on the computers. Only the principal investigator and the research assistant will have access to the documents. Each participant will have a personal identification code that can be used to connect the study material to the identifying data. The identifying data, consent forms and study material will be destroyed 10 years after the beginning of the study.

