### Adverse event reporting and harms {22}

Based on the literature and previous experience, only minor adverse events are expected. Any adverse events and harms reported to the research assistant will be discussed immediately within the research group.

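### Harms rest on unsolicited reports, and no check on prohibited own-use of magnesium or stockings is described, although a weekly form already reaches every participant

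*Protocol article*

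**What the plan says.** All references are to the Protocol article.

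- **Monitoring, {18a}:** "Any other symptoms, participant’s health or changes in the way of life will not be monitored during the follow-up". On the treatment period the same section adds: "The weekly reporting of the symptoms will continue using the same electronic questionnaire as previously".
- **Reach of the form, Confidentiality {27}:** "Participants will fill out the questionnaire themselves once every week for 8 weeks".
- **Harms, {11b} and {22}:** "Any harms reported to the research assistant will be recorded", and "Any adverse events and harms reported to the research assistant will be discussed immediately within the research group". Sections {11a} and {18b} tell participants to e-mail or phone the assistant if they have a problem.
- **Own-use, {11d}:** "The use of any magnesium products or compression stockings other than those used as the interventions of the study is prohibited during the trial". The next sentence says that other medications and supplements are recorded, without saying when or on what form.
- **Entry:** the exclusion criteria name "The use of a magnesium carbonate product" and "Continuous usage of compression stockings for any other reason than leg cramps". They name no other magnesium product, and no use of stockings for cramps.
- **Adherence:** Trial design {8} says participants' records cover adherence as well as symptoms. The Limitations section also refers to participants' own records of usage.

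**The concern.** The sentence in {18a} is a stated decision on what not to collect. It is not an omission that an analysis plan could repair later, because data never asked for cannot be recovered.

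For harms, the only route described starts with the participant. Follow-up is online with no appointments, so the weekly form is the one systematic contact with everyone. Stocking participants know their arm and have a built-in reason to write in, namely a wrong size. Tablet participants are blinded and have no such prompt. Reporting may therefore differ by arm for reasons unrelated to harm.

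For own-use, the prohibition applies to people who may have been using exactly these products. The Background says magnesium is commonly taken for cramps. One recruitment channel is the health-library article whose reader feedback mostly favoured stockings. If some participants go back to their own product and nobody asks, the arms may be drawn together and the analysis cannot show it.

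**Working it through.** **1. The plan's own figure.** The check needs the arm size, so the sample size {14} comes first. Inputs: one-way analysis of variance, three arms, f = 0.25, alpha 0.05, power 80%, drop-out 30%.

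- Noncentral F with noncentrality N × f²: 53 per arm (159 evaluable) gives power 0.805, and 52 per arm (156) gives 0.797.
- Inflation N / (1 − 0.30): 159 / 0.7 gives 228 when rounded up to equal arms, and 156 / 0.7 gives 223.
- The stated 225 lies between these. It leaves 225 × 0.7 = 157.5 evaluable, with power 0.801.

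So 225 reproduces, and 225 / 3 = 75 per arm. Nothing below changes it.

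**2. Harms.** Input: the diarrhoea rate of 1–2% for oral magnesium hydroxide in {11a}, assumed to apply to these 4 weeks. Expected cases = n × p × r, and P(at least one recorded) = 1 − (1 − p × r)^n, where r is the share of cases that reach the record. The article gives no value of r, so 30–70% is an assumption.

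- Full capture (r = 1): 75 × 0.01 = 0.75 and 75 × 0.02 = 1.5 cases. P = 1 − 0.99^75 = 0.53 and 1 − 0.98^75 = 0.78.
- Low end (p = 0.01, r = 0.3): 75 × 0.003 = 0.225 cases. P = 1 − 0.997^75 = 0.20.
- High end (p = 0.02, r = 0.7): 75 × 0.014 = 1.05 cases. P = 1 − 0.986^75 = 0.65.

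There is about one case to find. Under passive reporting, a record of none would say little.

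**3. Own-use, sections side by side.**

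- The exclusion criteria let in users of non-carbonate magnesium and people wearing stockings for cramps. Section {11d} then requires them to stop.
- Section {8} says adherence is recorded. Section {18a} reuses a form written for a period with no treatment to adhere to.
- Section {11d} records other supplements. The word follows directly on the sentence about magnesium and stockings, so it may leave those out.
- No section describes a question about the prohibited products in any of the 8 weeks.

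**4. What undetected own-use does.** The primary outcome {12} is the change from run-in to treatment period, so timing matters.

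- *Both periods:* a constant effect of the own product largely cancels in the change.
- *Run-in only:* the baseline count is altered. Participants do not yet know their arm, so this should balance across arms in expectation and mainly adds noise.
- *Treatment period only:* if a share c of the placebo arm resumes a product as effective as the study intervention, the contrast shrinks to (1 − c) of its value. The article gives neither c nor the effectiveness of the product, so no figure follows.

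**The case against.** **The case on the other side.** Reported harms are recorded and discussed at once, participants are told to make contact, the assistant writes to everyone weekly, and reasons for dropping out are analysed. Comparing safety is not an objective, since all listed outcomes concern cramps. Only minor events are expected, and the 12-person pilot saw no significant side effects. The magnesium and placebo tablets look identical, so knowledge of arm should not distort the diarrhoea comparison. The form itself is not shown, and the article may condense it.

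**Stronger readings that the article does not support.**

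- *Harms go uncounted.* Section {11b} provides for recording those reported. The problem is incomplete capture.
- *Own-use is ruled out of view.* The sentence in {18a} does not name supplements or adherence, and {8}, {11d} and the Limitations section touch on them. The firm statement is that no check on the prohibition is described.
- *The trial loses a known share of its effect.* That needs an own-use rate the article does not give, and an effective product. The article itself considers benefit from magnesium unlikely.
- *Reporting differs by arm.* This is possible, but nothing in the article shows it.

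**What stands.** Light monitoring is a disclosed choice, and with about one expected diarrhoea case even full capture would not support a formal safety comparison. But {18a} is an explicit negative, the form is stated to be unchanged between periods, and the entry criteria and the prohibition leave a group told to stop with no described follow-up.

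**Conclusion.** The point holds in a limited form, as a worthwhile and cheap improvement. As written, harms depend on unsolicited contact, so they are likely to be under-ascertained, possibly unequally between the stocking and tablet arms. The illustration is a chance of 0.20–0.65 of recording any diarrhoea case in the magnesium arm, against 0.53–0.78 with full capture. It rests on the article's 1–2% rate, 75 participants and an assumed 30–70% reporting share.

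On own-use, the article admits likely prior users, tells them to stop and describes no check. Use resumed in the treatment period would dilute the contrast to the extent that the product works. The size cannot be estimated, and without a record it cannot be examined afterwards. The sample size of 225 and the primary analysis are not called into question.

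**What to change.** 1. Reword the sentence in {18a} so that it agrees with {8} on adherence, {11b} and {22} on harms, and {11d} on supplements and prohibited products. State when and on what form the {11d} items are recorded.
2. Add two items to the existing weekly form, in all arms and both 4-week periods: (a) any new symptom or problem this week; (b) any use this week of magnesium or compression stockings other than those supplied by the study. Asking in the run-in gives each arm its own untreated background and shows whether own-use was continued or resumed.
3. Tabulate harms by arm as descriptive data, and report own-use by arm and period.

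An analysis adjusted for prior use should be added only if the baseline form is confirmed to record prior magnesium and stocking use, which the article does not clearly say.

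The cost is two questions, two short tables and slightly longer weekly reporting. Enrolment began in May 2021, so participants followed before the change would lack these items, and the report should say so.

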**Fig. 1 Fig1:**
[figure not shown]
Participant timeline

**Fig. 2 Fig2:**
[figure not shown]
Schedule of enrolment, interventions, and assessments

### Plans to promote participant retention and complete follow-up {18b}

Demographic data from all the participants will be collected through a baseline questionnaire. Weekly questionnaires are collected until possible discontinuation. In order to prevent dropouts, the research assistant will remind participants weekly by e-mail to fill out the questionnaire and will contact them if a weekly questionnaire is not returned. The participants will be instructed to communicate with the research assistant via e-mail or phone in case of any problems or questions related to the study.

### Data management {19}

All data will be collected electronically without any interphases by the participants through Microsoft Forms® electronic forms. Any Excel files will be formed without manual data recording.

### Confidentiality {27}

Material for the study will be collected using electronic questionnaires. Participants will fill out the questionnaire themselves once every week for 8 weeks. The consent forms that contain the participants’ names, birth dates or social security numbers, addresses, phone numbers and e-mail addresses will be sent to the principal investigator and stored in a locked cabinet of a locked office at the Unit of General Practice at Tampere University. The study material will be stored separately on secured computers, and it will not contain any information that could reveal the identity of the participants. In addition, the contact information form will be stored separately on the computers. Only the principal investigator and the research assistant will have access to the documents. Each participant will have a personal identification code that can be used to connect the study material to the identifying data. The identifying data, consent forms and study material will be destroyed 10 years after the beginning of the study.

### Plans for collection, laboratory evaluation and storage of biological specimens for genetic or molecular analysis in this trial/future use {33}

Not applicable, no samples collected.

## Statistical methods

### Statistical methods for primary and secondary outcomes {20a}

Descriptive statistics of the demographics will be displayed to ascertain any marked imbalance between the trial arms at baseline. The results of each of the three intervention groups will be analysed separately and compared. The primary comparative analysis will be conducted on an intention-to-treat-analysis.

The primary outcome will be the difference in the quantity of the leg cramps between the first and the second 4-week periods of the study comparing the three trial arms, and it will be analysed by one-way analysis of variance.

The secondary outcomes will be (1) the change in the intensity of the cramps between the first and the second 4-week periods of the study comparing the three trial arms and (2) the awakenings due to cramps between the first and the second 4-week periods of the study comparing the three trial arms. The difference between groups is analysed by a one-way analysis of variance of repeated measurements.

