### Outcomes {12}

#### Primary outcome

The change in the quantity of leg cramps from the 4-week follow-up period (prior to intervention) to the 4-week intervention period.

The change in the quantity of leg cramps will be assessed based on the participants’ responses to the electronic questionnaires. The quantity of cramps will be recorded using a weekly online survey during the 4 weeks before intervention and during the 4-week intervention period. The difference between the number of cramps from the 4-week period prior to the intervention to the intervention period will be calculated.

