### Participant timeline {13}

### Sample size {14}

The projected number of participants is based on sample size calculations, in which a power of 80% and significance level of 0.05 will show a difference between the intervention groups in the reduction of the quantity of leg cramps when variance analysis is used in statistical testing. The calculations for the minimum sample size are based on three of Cohen’s (1988) suggested effect sizes for *f* variance analysis. When the effect size of 0.25 and a drop-out rate of 30% are used, the number of applicable participants should be a minimum of 225 persons.

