## Assignment of interventions: allocation

### Sequence generation {16a}

After completing the baseline evaluation, eligible participants will be allocated to the compression stocking group, the magnesium group or the placebo group in a 1:1:1 ratio by an independent investigator using a computerised random number generator. The allocation will be stratified concerning age. To prevent selection bias, the research assistant who takes care of posting the interventions will be the only person to know each participant’s group assignment prior to treatment. The randomisation has strict limits regarding authority; no one can check the files except the principal investigator.

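### The primary one-way ANOVA of change leaves the baseline count and the age stratum out of the model; it is valid, but adding both as covariates would buy precision at no cost

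*Protocol article*

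**What the plan says.** The primary outcome section of the protocol article defines the outcome on the raw scale: "The difference between the number of cramps from the 4-week period prior to the intervention to the intervention period will be calculated". Section {20a} then names the test, "comparing the three trial arms, and it will be analysed by one-way analysis of variance". It mentions no covariate, stratum, transformation or count model. Section {20b} plans no additional analyses, and the only sensitivity analysis, in {20c}, concerns missing values.

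On randomisation, section {16a} says "The allocation will be stratified concerning age". The cut-points are not given, and age does not return in the analysis section.

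Section {14} powers the trial on the same variable and the same test: a difference "in the reduction of the quantity of leg cramps when variance analysis is used in statistical testing". The design and the analysis therefore agree with each other. The inclusion criteria set a minimum of 2 cramps a week and no maximum.

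**The concern.** Every participant spends 4 weeks recording cramps before treatment. A change score uses that information in one way only: it subtracts the baseline count, as if each extra cramp at baseline predicted exactly one extra cramp later. If the true slope is below 1, subtraction over-corrects and adds noise. ANCOVA estimates the slope from the data and removes that noise.

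Age was thought important enough to stratify on. A model that omits the stratum cannot use whatever age explains, and its standard error tends to be conservative for a stratified design.

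What is at stake is precision. The pilot study section names slow recruitment as the main challenge, and {14} allows for 30% drop-out. Precision from data that are already collected is worth having in such a trial.

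**Working it through.** **Inputs from the article.** Three equal arms ({16a}); "a power of 80% and significance level of 0.05 will show a difference between the intervention groups" ({14}); "When the effect size of 0.25 and a drop-out rate of 30% are used" ({14}); "the number of applicable participants should be a minimum of 225 persons" ({14}). The effect size f = 0.25 refers to the change in count. **Input not in the article:** the correlation r between baseline and intervention-period counts, taken here over 0.3 to 0.9.

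**Step 1: the plan's own figure.** For a one-way ANOVA with three arms, the F statistic has 2 and N − 3 degrees of freedom and noncentrality N × f². Power of 80% at f = 0.25 needs N = 157.2 evaluable participants. Dividing by 1 − 0.30 gives 157.2 / 0.70 = 224.6, so 225. (Rounding first to equal arms gives 159, then 228.) In reverse, 225 × 0.70 = 157.5 completers give 80.1% power. The stated figure reproduces.

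**Step 2: variance of the two analyses.** Let s1 and s2 be the standard deviations of the baseline and intervention-period counts within arm.

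- Change score: s1² + s2² − 2·r·s1·s2.
- ANCOVA residual: s2²·(1 − r²).
- Difference between them: (s1 − r·s2)².

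The difference is never negative, so apart from the degrees of freedom spent on covariates ANCOVA cannot be the less precise of the two. They tie only when the slope r·s2/s1 equals 1. With s1 = s2 = s the variances are 2s²(1 − r) and s²(1 − r²), and their ratio is (1 + r)/2, which is below 1 for every r below 1.

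**Step 3: power for the same raw effect.** The effective f becomes 0.25/√((1 + r)/2), and the noncentrality becomes 157.5 × 0.0625 / ((1 + r)/2) = 9.84 / ((1 + r)/2). One degree of freedom is spent on the covariate.

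| Assumed r | Variance ratio | Effective f | Noncentrality | Power, 157.5 completers | Enrolled N for 80% power |
|---|---|---|---|---|---|
| change ANOVA | 1 | 0.250 | 9.84 | 80.1% | 225 |
| 0.3 | 0.65 | 0.310 | 15.1 | 94.2% | 149 |
| 0.5 | 0.75 | 0.289 | 13.1 | 90.5% | 170 |
| 0.7 | 0.85 | 0.271 | 11.6 | 86.4% | 193 |
| 0.8 | 0.90 | 0.264 | 10.9 | 84.3% | 203 |
| 0.9 | 0.95 | 0.256 | 10.4 | 82.2% | 215 |

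The gain runs from about 14 percentage points at r = 0.3 to about 2 at r = 0.9.

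**Step 4: validity, and direction with skewed counts.** This step rests wholly on assumed parameters. Counts were simulated as Poisson with log-normal variation (median rate 12 per 4 weeks before the entry screen, log-SD between people 0.5 to 1.0 and between periods 0.3 to 0.5), entry at 8 or more cramps in 4 weeks, 52 completers per arm and 1,500 runs per setting. With no treatment effect, the change ANOVA rejected in 4.3% to 6.1% of runs, so it holds its level. With a rate ratio of 0.75 in one arm, power over four settings was 26% to 63% for the change ANOVA, 37% to 77% for ANCOVA on raw counts and 53% to 82% for ANCOVA on log(count + 1). The ordering was the same in all four settings. The levels of power say nothing about the planned f = 0.25, because the simulated standardised effect is a different one.

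**Age.** The article gives no relation between age and change in cramps, so no figure can be put on this part.

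**The case against.** The strongest reply is that nothing here is wrong. The trial was powered on the change in count with an analysis of variance, it analyses that variable with that test, and it reaches its stated 80%. Choosing between a change score and ANCOVA is choosing between two valid analyses, and if the two counts are highly correlated the gain is only about 2 points. All of this stands. The point is one of efficiency, and its size depends on a correlation that the article does not give.

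Four stronger readings are tempting, and the article does not support them:

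- *Chance baseline imbalance biases the result through regression to the mean.* Over repeated randomisations the change-score comparison is unbiased, and chance imbalance is already part of its standard error. It costs precision; it is not a systematic bias.
- *A few heavy crampers dominate the variance.* The entry rule has a floor and no ceiling, so a right tail is plausible, but the article gives no distribution.
- *The confidence interval ignores the stratified design.* Section {20a} states no confidence interval. Leaving out a stratification factor mainly makes standard errors conservative.
- *The primary analysis should move to the log scale.* That would replace the stated difference in cramps by a ratio and would depart from the sample size basis in {14}. It is a debatable choice, not a needed correction.

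A statistical analysis plan that is not shown could add covariates. The article, however, does not leave the matter open: it names the primary test outright.

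**Conclusion.** The concern holds as a loss of precision in a valid analysis. Neither the sample size nor the type I error is in question, and the baseline is used, though only by subtraction. With equal variances in the two periods, the change score has a larger error variance than ANCOVA for every correlation below 1: 33% larger at r = 0.5 (1/0.75) and 11% larger at r = 0.8 (1/0.90). At the planned effect size and about 157 completers, this means 80% power where about 82% to 94% was available for r between 0.9 and 0.3. The direction is secure. The size rests on the assumed r and on equal variances. The part due to age cannot be sized and may be small.

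**What to change.** In {20a}, replace the primary analysis sentence by wording such as: *The primary outcome will be analysed by analysis of covariance with trial arm as factor and the baseline 4-week cramp count and the age stratum used at randomisation as covariates. Adjusted differences in cramp count between arms will be reported.*

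With baseline in the model, the arm differences are identical whether the dependent variable is the change or the intervention-period count. The outcome definition in {12} and the effect measure therefore stay as they are. The 225 in {14} can stay too; it becomes somewhat conservative.

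Because the counts may be right-skewed, a log-scale or count-model analysis with the same covariates can be added as a prespecified sensitivity analysis. It need not replace the primary one.

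The cost is one or two sentences and a few degrees of freedom. No new data are needed: baseline counts are recorded before treatment, and age is known at randomisation. The change should be fixed before outcomes are examined by arm, so that the choice of covariates cannot appear to follow the results.

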#### Secondary outcomes

The change in intensity of leg cramps from the 4-week follow-up period (prior to intervention) to the 4-week intervention period.

The possible change in the intensity of leg cramps on a visual analogue scale from 1 to 10 will be assessed based on the participants’ responses to the electronic questionnaires. The intensity of cramps will be recorded using a weekly online survey during the 4 weeks before intervention and during the 4-week intervention period. The possible change in the intensity of cramps from the 4-week period prior to the intervention to the intervention period will be assessed.
2.The change in the quantity of nocturnal awakening due to the cramps from the 4-week follow-up period (prior to intervention) to the 4-week intervention period

The change in the quantity of nocturnal awakenings due to the cramps will be assessed based on the participants’ responses to the electronic questionnaires. The participants will record this data at the end of each week and are also instructed to keep their own cramp diary. The quantity of nocturnal awakening due to the cramps will be recorded using a weekly online survey during the 4 weeks before intervention and during the 4-week intervention period. The change in the number of nocturnal awakenings due to the cramps from the 4-week period prior to the intervention to the intervention period will be calculated.

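### The model named for the two secondary outcomes, a one-way repeated-measures ANOVA, does not by itself test change compared between the arms; the arm-by-period term is not stated

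*Protocol article*

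**What the plan says.** All of this is in the protocol article.

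- *Statistical methods {20a}* defines the first secondary outcome as "the change in the intensity of the cramps between the first and the second 4-week periods of the study comparing the three trial arms" and the second as "the awakenings due to cramps between the first and the second 4-week periods of the study comparing the three trial arms". It then names one method for both: "The difference between groups is analysed by a one-way analysis of variance of repeated measurements".
- *Secondary outcomes {12}* treats awakenings as a per-person change: "The change in the number of nocturnal awakenings due to the cramps from the 4-week period prior to the intervention to the intervention period" is to be calculated. Intensity and awakenings are both recorded weekly, for four weeks before and four weeks during the intervention.
- The primary outcome has the same before-to-during structure but a different method. The between-period difference is taken, "comparing the three trial arms, and it will be analysed by one-way analysis of variance".
- *Trial design {8}* frames the trial as superiority between the arms, and *Objectives {7}* lists intensity and awakenings beside frequency as main outcomes.
- *Additional analyses {20b}* plans none.

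No section names an arm-by-period (or arm-by-week) interaction, a mixed model or a baseline-adjusted comparison for the secondary outcomes.

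**The concern.** The question for each secondary outcome is whether the change from baseline differs between three arms. With two periods, the term that answers it is the arm-by-period interaction, which gives the same F as a one-way ANOVA of the change scores.

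In standard usage, a one-way repeated-measures ANOVA has one factor, measured within person. Here that factor would be period (or week), and its F asks whether the second four weeks differ from the first for everyone together. If one-way instead refers to arm, with two values per person, the factor's main effect compares arms on the average of both periods. One of those periods is untreated, so no effect of treatment can appear in it.

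An analyst who took the label at face value could therefore report one of two wrong F statistics. The first responds to improvement shared by all arms. Such improvement is plausible: participants are enrolled because they are currently symptomatic, outcomes are self-reported, and the stocking arm is not blinded. The second dilutes a real arm difference.

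**Working it through.** **1. The plan's own figure.** *Sample size {14}* asks that "a power of 80% and significance level of 0.05 will show a difference between the intervention groups", and continues: "When the effect size of 0.25 and a drop-out rate of 30% are used, the number of applicable participants should be a minimum of 225". For a one-way ANOVA with k = 3, the noncentrality is λ = f²N. The smallest N with at least 80% power is 158 (power 0.802), and 158 / 0.7 = 225.7, i.e. 226. The stated 225 is reproduced to within one person. It rests on a comparison between arms, so nothing below changes it.

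**2. Inputs for the illustration.**
- Analysed per arm: 225 × 0.7 / 3 = 52.5, taken as 52 (N = 156). Allocation is "in a 1:1:1 ratio by an independent investigator using a computerised random number generator".
- Assumed, because the documents give neither: SD 1 in each period and within-person correlation ρ = 0.5. Normal outcomes are also assumed.
- SD of the change: √(2(1 − ρ)) = 1.
- SD of the mean of both periods: √((1 + ρ)/2) = 0.866.
- Residual SD after baseline adjustment: √(1 − ρ²) = 0.866.

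**3. Period test, no arm difference.** z = fall × √N / SD of change.
- Fall of 0.2 SD: 0.2 × √156 = 2.50, significant in about 70% of trials.
- Fall of 0.4 SD: 0.4 × √156 = 5.00, significant in about 99.9% of trials.

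The arm-by-period test stays at 5% in both cases.

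**4. True effect of 0.53 SD in one of three arms.** The arm means have SD 0.53 × √2/3 = 0.250.
- Arm-by-period, or ANOVA on change: f = 0.250 / 1 = 0.25, which is the protocol's own design effect; λ = 9.7; power about 80%.
- Arm main effect over both periods: f = (0.250 / 2) / 0.866 = 0.144; λ = 3.2; power about 33% (34% by noncentral F, 33% simulated). The raw difference is halved. The standardised effect falls to 0.5 / 0.866 = 0.58 of its value.
- ANCOVA on the intervention-period value adjusted for baseline: f = 0.250 / 0.866 = 0.288; λ = 13.0; power about 90%.

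**5. Range over the assumed correlation** (N = 156; same falls and same 0.53 SD effect, same formulas):

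| ρ | Period test, fall 0.2 / 0.4 SD | Arm main effect | Arm-by-period | ANCOVA |
|---|---|---|---|---|
| 0.3 | 56% / 99% | 39% | 64% | 83% |
| 0.5 | 70% / 99.9% | 34% | 80% | 90% |
| 0.7 | 89% / >99.9% | 30% | 96% | 98% |

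**6. Separate simulation** (5,000 trials per scenario, 53 per arm, ρ = 0.5).
- All arms fall by 0.3 SD: period test 96%, arm-by-period 5%.
- Arms differ (f = 0.25 on change) with average change zero: period test 4.5%, arm main effect 34%, arm-by-period 81%.

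The period test thus fails in both directions as a test between arms.

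**The case against.** The best reply is that the sentence says what it is for. Its subject is the difference between groups, and both outcome definitions compare the three arms. A model without an arm factor cannot be what the authors wanted. On this view one-way means one between-person factor (arm) with repeated measurements, and the outcome definitions point to the arm-by-period term. With two periods that is the primary outcome's analysis under another name, with about 80% power in the illustration.

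Much of this stands. The mixed design is a plausible intention, and a reader should not infer that the trial cannot answer the between-arm question or that false positive secondary results are to be expected. The 70% to 99.9% figures arise only if arm is left out and the pooled period effect is reported as an arm difference. The 33% figure arises only if the main effect is the one chosen. The text requires neither, and the SD, correlation and common fall are assumed.

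What does not stand is that the matter is only detail left to an analysis plan. The article does not leave the method open: it names one, and in its usual meaning that method lacks the term the outcome needs. It also departs from the primary outcome's method without giving a reason. Even on the kinder reading of one-way, the term to be tested is not given.

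**Conclusion.** The stated method does not match the stated question for the two secondary outcomes. The mismatch is structural and does not depend on the assumed figures; only its numerical size does. If the wrong term were used, the cost would range from a test that reacts to any shared improvement (about 70% to 99.9% rejection for common falls of 0.2 to 0.4 SD at ρ = 0.5) to a between-arm test with about 33% power where 80% was available. If the arm-by-period term was meant and is used, nothing is lost beyond the unclear label.

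A reader might extend the point to the primary outcome or to the sample size. The documents do not support that: the primary analysis compares arms on change, and 225 reproduces from that ANOVA. Nor are the interaction test and ANCOVA the same test. Both address the between-arm question, but their power differs (80% against 90% here). This is a should-fix point confined to the secondary outcomes.

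**What to change.** Replace the sentence on the secondary outcomes with, for example: *Each secondary outcome will be compared between the three arms by analysis of covariance of the 4-week intervention-period value, adjusted for the 4-week baseline value.*

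The minimum acceptable alternative is either a one-way ANOVA on the change, which matches the primary outcome, or a mixed model whose stated test is the arm-by-period interaction. ANCOVA is preferred for its power, but any of the three removes the mismatch.

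The cost is wording only. The weekly data already planned are sufficient, and the sample size and primary analysis stay as they are. As enrolment has begun (*Trial status*), the clarification should be dated and recorded before the statisticians' group codes are broken.
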